Obesity often results from an imbalance between too little energy expenditure and too much energy intake [14]. Therefore, to achieve weight loss as a primary goal, obesity interventions should help individuals be more physically active and eat healthier. Moreover, various studies indicate that obesity is negatively associated with indicators of health-related quality of life [15]. Individuals with obesity often report that because of their weight they experience physical complaints, have problems during their daily activities, or have difficulties to move in public [16]. In the same vein, individuals with obesity report often experiencing negative affective states, such as anger, fear or shame, in their daily life [17]. Because indicators of health-related quality of life are associated with the use of health services [18] as well as mortality [19], they are also important indicators of the success of an obesity intervention.

To increase the effectiveness of obesity interventions it is further important to understand the psychological processes that are associated with behaviour change [20]. In this study, we focus on the psychological processes related to physical activity. In this regard, a large number of studies shows that individuals who have a more autonomous motivation are more likely to be physically active [21]. In addition, dual-process theories that attempt to explain physical activity behaviour emphasize the role of both more explicit as well as more implicit psychological processes [22, 23]. On the one hand, individuals’ intention, self-efficacy, and enjoyment towards physical activity as more explicit processes have been consistently associated with physical activity [24–26]. On the other hand, habit is considered a more implicit process that has also been shown to be associated with physical activity [27].

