To summarize, the high prevalence of obesity is a major problem from both an individual and societal perspective [1]. While mHealth interventions may provide new promising ways to combat obesity, scientific evidence of their effectiveness is still sparse [11]. Therefore, the primary purpose of this study is to evaluate the effectiveness of an mHealth obesity intervention by assessing body weight as well as indicators of physical activity, eating behaviours and health-related quality of life. In addition, the secondary purpose of this study is to assess more explicit (i.e., motivation, intention, self-efficacy, enjoyment) and more implicit (i.e., habit) psychological processes associated with physical activity behaviour change through the use of mixed methods.

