### Methods

#### Sampling and participants

The patients are recruited from obesity centres across Germany. Currently, the participants will be recruited from seven obesity centres and it is possible that more obesity centres will participate. Of the seven obesity centres, four offer an mHealth intervention and three do not. The inclusion criteria are that patients are at least 18 years old, have a basic knowledge of the German language, and a BMI ≥ 30. During their first stay at the obesity centre, patients will be asked to participate in the study. Due to the nature of the study, neither participants nor staff can be blinded to allocation. Thus, patients attending an obesity centre that offers an mHealth intervention will be asked whether they want to take part in the mHealth intervention. The patients who agree to take part in such an intervention will be assigned to the intervention group, while those who do not want to take part in such an intervention will be assigned to the control group. Moreover, patients attending a obesity centre that does not offer mHealth interventions will be assigned to the control group. The patients will receive no financial compensation for their participation in the study.

Given the insufficient evidence for the effectiveness of mHealth obesity interventions [28], a small effect size was considered in the power analysis. Conservatively estimating the effect size by *η*^2^ = 0.01, *α* = 0.05, 1-*β* = 0.80, with two groups, a correlation on among repeated measures of *r* = .30 and a design with three repeated measurement occasions, using an ANOVA with repeated measurements (within-between interaction), the calculated total sample size is 225 participants, nearly equally distributed over two groups. Since we expect a dropout rate of about 50% [29], the plan is to recruit 450 patients.

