### Data analysis

#### Data analysis of quantitative data

All data related to personal information will be pseudo-anonymized. Data will be entered by a research assistant and checked independently for their accuracy by another research assistant. Multiple imputation or the full-information maximum likelihood approach will be employed to treat missing data [47]. We will conduct two analyses: (a) with all patients who agreed to participate in the intervention and (b) with only those patients who completed the intervention (i.e., they had three stays at an obesity centre). A multivariate analysis of variance with repeated measurements (2 groups x 3 time points) will be used to analyze the effects of the intervention on the dependent variables (i.e., body weight, physical activity, eating style & behaviour, health-related quality of life). For the analysis of the structure of determinants of physical activity (i.e., motivation, intention, self-efficacy, enjoyment, habit) and its interdependencies, structural equation modeling procedures will be applied. In particular, the development of the dependent variables will be analyzed using latent growth curve models [48]. Moreover, mediation analyses will be conducted to test whether the determinants of physical activity mediate the effects of the intervention on physical activity behaviour. The effects of age, gender, frequency of participation in the mHealth application (supplied by the provider), and the physical activity level outside of the intervention will be controlled.

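### The 80% power belongs to a one-outcome ANOVA, but effectiveness is tested by a MANOVA over about nine scores with no primary outcome, so the stated power does not apply and a significant result need not concern weight

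*Protocol article*

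**What the plan says.** Under Sampling and participants, the effect size and error rates are given as "Conservatively estimating the effect size by *η*^2^ = 0.01, *α* = 0.05, 1-*β* = 0.80, with two groups", with "a correlation on among repeated measures of *r* = .30" and "a design with three repeated measurement occasions". The test is named there: "using an ANOVA with repeated measurements (within-between interaction), the calculated total sample size is 225 participants", and the patients are "nearly equally distributed over two groups". An expected dropout of about 50% takes 225 to a recruitment target of 450. The outcome to which the effect size refers is not named.

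Under Data analysis of quantitative data, the effectiveness test is a different one: "A multivariate analysis of variance with repeated measurements (2 groups x 3 time points) will be used to analyze the effects of the intervention". Its dependent variables are body weight, physical activity, eating style and behaviour, and health-related quality of life.

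The Background puts all four domains under one purpose: "the primary purpose of this study is to evaluate the effectiveness of an mHealth obesity intervention by assessing body weight as well as indicators" of the other three. The first objective in the Discussion groups them in the same way. Neither place singles out a primary outcome.

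**The concern.** A sample-size statement is a promise about a particular test. Here the promise is made for one test and the analysis section names another, with many more degrees of freedom and a different null hypothesis. The interaction hypothesis of the MANOVA is that no score changes differently between the groups. Rejecting it says that something moved, not what. A reader of the final report would reasonably take a positive effectiveness test as evidence on weight, which comes first in every statement of purpose (Abstract, Background, analysis section, Discussion). As the plan stands, that inference is not licensed, and the chance of detecting a weight effect is not known.

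**Working it through.** **1. Reproduce 225.** Inputs from Sampling and participants: η² = 0.01, α = 0.05, two groups (k = 2), three occasions (m = 3), r = 0.30.

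- f² = η²/(1 − η²) = 0.01/0.99 = 0.0101
- λ = f²·N·m/(1 − r) = 0.0101 × 225 × 3/0.70 = 9.74
- df1 = (k − 1)(m − 1) = 2; df2 = (N − k)(m − 1) = 223 × 2 = 446
- Power from the noncentral F distribution: 80.2%

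N = 225 is the smallest size that reaches 80%, and 225/(1 − 0.5) = 450. Both stated figures reproduce, but for one outcome and 2 degrees of freedom.

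**2. Count the scores in the planned test.** From the instrument sections: body weight 1, GPAQ activity 1, HESQ 1, DEBQ 2 (emotional, external), SF-12 2 (physical, mental), PANAS 2 (positive, negative). That is nine, or ten if GPAQ sedentary time is counted. PANAS is included because the protocol places it under health-related quality of life. With two time contrasts per score, the interaction has 2 × 9 = 18 degrees of freedom.

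**3. Power of the MANOVA at N = 225.** With two groups, the test is a Hotelling T² on p outcomes × 2 time contrasts: df1 = 2p = 18, df2 = N − 2p − 1 = 206. Each affected outcome carries the plan's own λ = 9.74. The total noncentrality is λ·e′R⁻¹e, where e marks the affected outcomes (same standardised effect, in the direction of the positive correlation) and R has a common correlation ρ between outcomes. The documents give no ρ, so 0 to 0.7 is an assumed range. As a check, p = 1 returns 79.9%, close to step 1.

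| ρ (assumed) | weight only | weight + 1 other | all nine equally |
|---|---|---|---|
| 0 | 38% | 75% | ~100% |
| 0.2 | 45% | 78% | 96% |
| 0.3 | 51% | 83% | 88% |
| 0.5 | 69% | 95% | 69% |
| 0.7 | 93% | ~100% | 53% |

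The weight-only figure at ρ = 0 barely depends on the count: 41% with eight scores, 36% with ten.

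**4. Significance without a weight effect.** Set the weight effect to zero and ρ = 0. If two other scales have the planned effect, λ = 19.48 and the MANOVA is significant with probability 75%. If four do, λ = 38.96 and the probability is 98%.

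**5. Alternative reading: separate analyses.** If the multivariate wording meant the multivariate approach to repeated measures run outcome by outcome, power per outcome is 79.9% and the mismatch in power disappears. There would then be about nine tests, still with none primary.

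**The case against.** The strongest reply is that the mismatch need not mean low power. The Background expects activity and eating to act on weight, so several outcomes may move together; two affected outcomes at ρ = 0.3 already give 83%. This stands. A reader might infer from the 38% that the study is badly underpowered, but that figure is one corner of the table: a single responding outcome, uncorrelated with eight others. What the documents support is that the power of the named test is unstated and depends on inputs they do not give.

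A reader might also infer an inflated error rate, since nine independent tests at 5% give 1 − 0.95⁹ = 37%. That does not describe a MANOVA, which is one test at 5%, and the article specifies no univariate follow-up tests. The figure could arise only under the separate-tests reading, where the power mismatch disappears. The two criticisms cannot both be charged to the plan.

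It is tempting to add that r = 0.30 is too low for body weight and hence that 225 is wrong. The documents give no correlation for weight, and at fixed η² a higher r raises power: at r = 0.50 the same formula needs 161 patients, not 225.

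The Background phrase "to achieve weight loss as a primary goal" might be read as naming the primary endpoint. In context it describes obesity interventions in general.

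Finally, the Abstract names latent growth curve models beside the MANOVA for comparing the groups, so inference on weight might come by that route. But those models are not designated as the primary test either, and the 225 was not calculated for them. Nor can the issue be left to an analysis plan that is not shown: the article itself states both the powered test and the effectiveness test, and they differ.

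**Conclusion.** The concern holds in this form: the 80% power is correct for a one-outcome interaction test and is not a property of the MANOVA named for effectiveness, and no outcome is primary. With the plan's effect size and 225 patients, weight-only power lies between about 38% and 93% for assumed correlations of 0 to 0.7, and can be above or below 80% when several outcomes respond. A significant MANOVA does not establish a weight effect; in the uncorrelated case with two other responding scales, it occurs about 75% of the time without one.

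The difference between the two tests and the absence of a primary outcome are read directly from the text. The percentages rest on nine scores, equal standardised effects, a common between-outcome correlation and roughly equal groups. The analysis section's wording favours the joint reading, but under either reading a primary outcome is needed.

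**What to change.** Designate one primary outcome. Body weight is the natural choice, being listed first in every statement of purpose. Give it a single univariate group-by-time test at 5%. Make the activity, eating and quality-of-life scores secondary, and keep the MANOVA as a supportive analysis.

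Restate the 80% power as applying to the primary test only, with the effect on that outcome's own scale and the SD and correlation labelled as assumptions. For illustration, take change in weight from baseline to one follow-up, with 225 patients split equally (112.5 per group). The detectable difference is (1.96 + 0.84) × SD × √(2/112.5). For an assumed SD of change of 6, 8 or 10 kg this gives 2.2, 3.0 or 3.7 kg, before any allowance for clustering by centre or unequal groups. The documents give no SD, so the authors must supply and justify one; if the two-degree-of-freedom interaction is kept as the primary test, the figure must be recalculated for it.

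The cost is a change of wording in the outcomes, sample-size and analysis sections, with no more patients. The real price is that the other scales lose co-primary standing. Dropping the MANOVA altogether, or adding a formal multiplicity procedure for the secondary outcomes, is optional.

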#### Global physical activity questionnaire

Physical activity will be assessed with the Global Physical Activity Questionnaire (GPAQ) [30]. The GPAQ consists of 16 items measuring volume and intensity of moderate and vigorous intensity in the areas of work, transport, and discretionary time. Moreover, the GPAQ measures daily sedentary time. The GPAQ has been shown to have a 10-days test-retest reliability of *r* = .83 to *r* = .96 and a 3-months test-retest-reliability of *r* = .53 to *r* = .83 [31]. The GPAQ also shows a moderate agreement with accelerometer measures [32].

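### CASPAR use, which is the treatment dose, is listed as a control variable without restriction, and outside activity is listed with no time point

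*Protocol article*

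**What the plan says.** Under *Data analysis of quantitative data*, the protocol article plans a repeated-measures MANOVA (2 groups, 3 occasions) for the intervention's effect on weight, physical activity, eating and quality of life. Structural equation and latent growth curve models follow, and then: "mediation analyses will be conducted to test whether the determinants of physical activity mediate the effects of the intervention on physical activity behaviour". The last sentence of the section names the control variables. After age and gender it adds: "frequency of participation in the mHealth application (supplied by the provider), and the physical activity level outside of the intervention will be controlled". It does not say which of the models this covers.

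Other sections fix what these two variables can be:

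- *mHealth obesity intervention*: CASPAR is the digital supervision between stays, with a target of up to 90 minutes a week over 24 weeks.
- *Quantitative data collection methods*: baseline is taken during the first stay, before that period.
- *Sampling and participants* and *Control group*: controls either declined the mHealth option or attended a centre without it.
- *Global physical activity questionnaire*: the only physical activity instrument listed is described as "measuring volume and intensity of moderate and vigorous intensity in the areas of work, transport, and discretionary time". The text after Fig. 1 has it administered at baseline and at both follow-ups.

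**The concern.** A covariate in an effectiveness model should be fixed before treatment or be unaffected by it. CASPAR use is neither. It is the treatment measured as a quantity, and only one group can have any. It cannot be a common cause of group and outcome, so controlling it does nothing for the selection bias that the *Discussion* admits. What it does is change the question. The group coefficient becomes the difference between controls and patients who joined the intervention group but used the application for zero minutes. The *Background* gives effectiveness of the intervention as the primary purpose, and this contrast is not that.

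Activity outside the intervention raises a second question, because physical activity is both a declared outcome and, according to the *Background*, a route by which obesity interventions bring about weight loss.

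At stake is the main comparison. A working intervention could show a shrunken or imprecise group effect for reasons that lie in the model.

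**Working it through.** **1. The plan's own figure.** *Sampling and participants* powers the study "using an ANOVA with repeated measurements (within-between interaction"), with η² = 0.01, r = 0.30, two groups, three occasions, α = 0.05 and power 0.80.

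- f² = 0.01/0.99 = 0.0101
- λ = f² × N × 3/(1 − 0.30). At N = 225, λ = 0.0101 × 675/0.70 = 9.74.
- df = 2 and (225 − 2) × 2 = 446; power is 0.802.

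The stated 225 reproduces, and 225/(1 − 0.50) = 450. No covariate is mentioned, so this power describes an unadjusted group-by-time test.

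**2. Collinearity of use with group.** Let G be 0 or 1 with equal groups. Use is 0 in controls; in the intervention group it has mean μ and coefficient of variation CV.

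- Var(G) = 1/4
- Cov(G, use) = μ/4
- Var(use) = μ²(1/4 + CV²/2)
- R² = (1/16) / [(1/4)(1/4 + CV²/2)] = 1/(1 + 2CV²)
- Variance inflation = 1/(1 − R²) = 1 + 1/(2CV²)

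| Assumed CV of use | R² | Variance inflation | SE multiplier | 225 patients are worth about |
|---|---|---|---|---|
| 0.5 | 0.67 | 3.0 | 1.73 | 225/3 = 75 |
| 1.0 | 0.33 | 1.5 | 1.22 | 225/1.5 = 150 |

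The documents give no CV, so both rows are assumptions. In a repeated-measures MANOVA a covariate has its own coefficient at each occasion, so the same inflation applies to contrasts of change.

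**3. Bias and power by mediated share.** This is a simulation of one follow-up outcome: N = 225, 2,000 runs per scenario. The assumed total effect is −0.40 SD, and assumed use in the intervention group has mean 65 and SD 25 minutes a week. The CV is 25/65 = 0.38, so variance inflation is 1 + 1/(2 × 0.148) = 4.4 and the SE multiplier about 2.1.

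| Share of effect through use | Group only: estimate (SE), rejection rate | With use added: estimate (SE), rejection rate |
|---|---|---|
| All | −0.40 (0.13), 0.85 | −0.01 (0.28), 0.05 |
| Half | −0.41 (0.13), 0.86 | −0.21 (0.28), 0.13 |
| None | −0.40 (0.13), 0.84 | −0.40 (0.28), 0.30 |

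The adjusted estimate is the total effect times (1 − share through use), up to simulation error. In the last row there is no bias, and the loss is precision alone.

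**4. Outside activity, if taken at follow-up.** Suppose treatment raises it by 0.5 SD and its coefficient on the outcome is −0.3. It then carries 0.5 × (−0.3) = −0.15, for a total of −0.40 − 0.15 = −0.55. Adjusting for it returns about −0.40. A baseline value cannot carry any of the effect.

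**The case against.** **Scope.** The MANOVA is specified earlier in the section with no covariates, the power calculation has none, and the covariate sentence directly follows the mediation sentence. A reader could take it to govern only the mediation and structural models. Equally, a reader might infer that the primary MANOVA is certainly adjusted. The text settles neither. The narrow reading does not rescue the plan, however: in the mediation model, controlling use blocks the path from intervention to the determinants of activity.

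**Size.** A reader might infer that the adjustment wipes out the effect. That holds only if the whole effect runs through use, a condition that a simulation can build in but the documents do not supply. With no mediation through use, the estimate is unbiased. This objection stands, which is why the result is given as a range.

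**Outside activity.** It is tempting to say that this variable is measured after baseline and forms part of the GPAQ outcome. The article gives it no time point, instrument or definition. A baseline GPAQ value will exist, and in a self-selected comparison prior activity is a plausible confounder. This objection also stands, so that half of the point is conditional.

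**The contrast.** One might describe the adjusted coefficient as the effect of being offered CASPAR and not using it. That is not right here, because patients who are offered it and decline become controls. Membership of the intervention group means agreement.

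**Conclusion.** The point holds for CASPAR use and should be corrected before analysis. As written, a post-baseline measure of treatment dose, zero for all controls, may enter any between-group model. The consequences are:

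- **Estimand:** the group coefficient becomes the contrast at zero use.
- **Bias:** the share of the effect that runs through use is lost, from none to all. The documents do not allow that share to be estimated.
- **Precision:** the standard error rises 1.73-fold at a CV of 0.5 and 1.22-fold at 1.0, whatever the share. This assumes roughly equal groups, as the sample size section does, and a linear covariate effect.

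For outside activity the finding is an ambiguity with a harmful reading (follow-up activity) and a legitimate one (baseline activity). The sample size of 225 is not in question. It reproduces, but it does not describe a model that includes CASPAR use.

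**What to change.** Amend the last sentence of *Data analysis of quantitative data* so that it says the following:

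- CASPAR participation does not enter any model that estimates a between-group effect, whether MANOVA, growth curve or mediation. It is used only in a dose-response analysis within the intervention group, labelled exploratory because patients choose their own level of use.
- Any physical activity covariate is the baseline GPAQ value, and it is used for outcomes other than physical activity. For physical activity itself, baseline is already one of the three occasions in the model.
- Age and gender stay. The list is not closed to other pre-treatment factors. Centre and programme differences in particular should remain open to adjustment, since the *Control group* section describes them and the *Discussion* names them as possible confounding.

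The cost is a few sentences of text. No data item, visit or patient is affected, and the sample size calculation is unchanged.

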#### Data analysis of qualitative data

After a verbatim transcription of the interviews, a reflexive thematic analysis approach will be used. Such an approach acknowledges that themes are actively generated by researchers resulting from their engagement with the data [49]. In particular, the analysis will follow the recursive six-phase model proposed by Braun and colleagues [50]. To ensure the rigour of the qualitative study, the data analysis will be carried out independently by two researchers. Moreover, other researchers in the team will act as critical friends helping consider alternative interpretations of the answers [51].

